# treatment

## Method(s) of assigning patients to treatment groups

All patients will initially receive ABR-215757 administered perorally at 3.0 mg/day once daily.

## Treatment administration

### Selection and Timing of Dose for each patient

All patients will initially receive an oral dose (3.0 mg) of study drug once daily for 8 weeks. The dose may be reduced to 1.5 mg/day depending on the tolerability of ABR-215757 in individual patients. The first dose of study medication will be taken at the clinic after all baseline assessments have been completed. At all visits to the clinic, the daily dose of study medication should be taken at the clinic, and after all assessments have been completed. There are no additional dosing instructions with respect to meal times, or to the dosing schedules of other medications.

## Blinding

Not applicable in this study

## Prior and Concomitant Therapy

All concomitant medication (including start/stop dates and indication) must be recorded in the patient’s source documentation as well as in the appropriate pages of the CRF.

### Contraception

Sexually active women of child-bearing potential are required to use a reliable method of contraception. Because of the lack of clinical studies investigating the potential risk of interaction between ABR-215757 and hormonal (oral or depot) contraceptives, women using such products must also use additional contraception, including at least one barrier method.

### Restrictions in prior and concomitant therapy

The following medications and therapies are not allowed before and during the study including the follow-up period:

- Other investigational agents, *ie* any drug not approved for sale in the country in which it is being used, within 4 months or 5 half lives (whichever is longer) prior to the first dose of study medication.
- Oral treatment with corticosteroids (>10 mg/day prednisolone or equivalent) or changes in corticosteroid dosing within 8 weeks prior to the first dose of study medication and during the study. Inhaled, intraarticular or topical steroids may be given for reasons other than SSc disease activity (such as asthma, contact dermatitis) as clinically indicated.
- Mycophenolate mofetil (MMF) or Cyclophosphamide within 6 months, Methotrexate, Azathioprine or other immunosuppressants within 3 months prior to the first dose of study medication.
- Rituximab within 12 months or other biologics within 6 months prior to first dose of study medication.
- Intravenous corticosteroids within 3 months prior to the first dose of study medication.
- Potent inhibitors of CYP 3A4 intravenously or orally administered within 14 days prior to the first dose of study medication. ABR 215757 is eliminated almost exclusively by metabolism mediated by CYP 3A4. In vitro studies reveal that ABR-215757 metabolism can be inhibited by potent CYP 3A4 inhibitors. It is therefore expected that drugs which are potent inhibitors of CYP3A4 lead to an increase of ABR-215757 blood concentrations and are therefore not allowed.
  Potent CYP3A4 inhibitors include drugs like the imidazoles (e.g. ketoconcazole), macrolides (e.g., erythromycin) and protease inhibitors (e.g., ritonavir). Furthermore, potent inducers of CYP3A4 (e.g. rifampicin, rifabutin, phenytoin, carbamazepin, St John’s wort), may lead to a decrease of ABR-215757 blood concentrations. Concomitant medication with these inducers should therefore be avoided.
- Endothelin receptor antagonists within 6 weeks prior to the first dose of study medication
- Medications that prolong the QT/QTc interval.
- Vaccination within 4 weeks prior to the first dose of study medication.

The following medications may be used only at stable dose within 2 weeks before the first dose of study medication and throughout the study including the follow-up period:

- Oral calcium channel antagonists
- Phosphodiesterase inhibitors
- Proton pump inhibitors

## Treatment Compliance

The number of capsules issued to each patient will be entered into the CRF at visits 2 and 4. Study medication accountability and review of treatment compliance will be performed at visits 4 and 5. Retrieval of unused study medication and final drug accountability will be performed at visit 5. Noncompliance is generally defined as more than 14 missed doses during the study.

# EFFICACY AND SAFETY VARIABLES

The timing of individual assessments is presented in the Schedule of Investigational Events (appendix 1).

## Biomarker Measurements

Blood samples and skin biopsies will be taken for assessment of a number of disease related biomarkers. Punch biopsies (diameter 4 mm, two biopsies per patient at indicated visits) will be obtained from lesional skin of the forearm. Assessments will include markers of fibrosis vasculopathy and immune activation. Unless otherwise indicated, all assessments will be performed by a central laboratory. Details of sample preparation and analyses will be provided in a separate document. A number of exploratory markers that may have implications for the pathology of SSc or the mode of action of ABR-215757 will be evaluated.

## Disease Activity Measurements

Disease activity measurements will include the following assessments

- Modified Rodnan Skin Score (mRSS)
- Digital ulcers

## Quality of life

The quality of life will be assessed using SF-36 Health Survey and Scleroderma Health Assessment Questionnaire (SHAQ)

## Drug concentration Measurements

Blood samples to determine the plasma levels of ABR-215757 will be collected from all patients receiving treatment and at all visits from the baseline visit (day 0) until visit 6 (follow-up visit).

Blood samples will be drawn by venous puncture or indwelling venous catheter into sodium- or lithium heparinized Vacutainers®.

The date and exact time point of the blood sampling will be recorded on the CRF. The date and time of the last dose prior to sampling will also be noted on the CRF.

Details of sample preparation and analyses will be provided in a separate document.

## Safety variables

### Definition of Safety Variables

Safety variables monitored throughout the study will include:

- Adverse events
- Safety laboratory evaluations
- Physical examination
- Vital signs
- ECG

### Safety Measurements

#### Safety Laboratory Evaluations

All safety laboratory analyses will be performed by the local hospital laboratory, reference ranges will be supplied by the local laboratory and used by the investigator to assess the laboratory data for clinical significance and pathological changes.

***Hematology:***

Hemoglobin, WBC, platelet count, ESR. Samples will be taken at visits 1 - 6

***Clinical Chemistry:***

Sodium, potassium, aspartate-amino-transferase (ASAT/GOT), alanine-amino-transferase (ALAT/GPT), alkaline phosphatase (ALP), gamma-glutamyl-transferase (GGT), pancreatic amylase, creatinine, total biliru­bin, calcium, albumin, C-reactive protein (CRP). Visits 1 – 6 will include all above clinical chemistry assessments. For patients that participate in the continuation phase, assessments will include ASAT/GOT, ALAT/GPT, ALP, GGT, bilirubin and CRP.

***Coagulation:***

Fibrinogen (FIBR) Samples will be taken at visits 1 - 6.

***Urin­aly­sis:***

Leukocytes, protein (or albumin) and blood (erythrocytes). Samples will be taken at visits 1,2,4,5 and 6

***Other Laboratory variables***

Urine pregnancy tests will be performed in females of childbearing potential. Samples will be taken at visits 1, 2, 4, 5, 6 and at all visits of the continuation phase as applicable.

#### Physical Examination

A complete physical examination will be performed with review of body systems (eyes, ears, nose and throat, cardiac, peripheral vas­cular, pulmonary, muscu­los­keletal, neurolo­gic, abdomi­nal, lymphatic, dermatologic). Physical examination will be performed at visits 1 and 6.

#### Vital Signs

Vital signs, including: weight, height (baseline only), blood pressure, heart rate, and body temperature will be documented. Supine blood pressure (systolic and diastolic) and pulse rate (over 1 minute) are to be measured in the same arm after a five-minute rest. The same method and the same cuff size should be used to measure blood pressure in each individual patient throughout the study. Vital signs will be recorded at visits 1 - 6.

#### ECG

12-lead ECG after a five-minute rest will be recorded before, during and after treatment, and will be assessed at the study clinic. The ECG result (including heart rate, PR/PQ, QRS, QT (incl. QTc), and S-T intervals) will also be manually evaluated by a central ECG reader. ECG will be measured at visits 1, 2, 5 and 6

### Adverse Events

#### Definitions

An adverse event (AE) is any untoward medical occurrence in a patient or clinical investigation subject administered a pharmaceutical product (or using a medical device) and which does not necessarily have a causal relationship with that treatment or usage.

***Adverse events include the following:***

a) All suspected adverse medicationreactions.

b) All reactions from medication overdose, abuse, withdrawal, sensitivity, or toxicity

c) Apparently unrelated illnesses, including the worsening of a pre-existing illness (see *Pre-existing Conditions*, below).

d) Injury or accidents. *Note* that if a medical condition is known to have caused the injury or accident (e.g., a fall secondary to dizziness), the medical condition (dizziness) and the accident (fall) should be reported as two separate adverse events. The outcome of the accident (e.g., hip fracture secondary to the fall) should be recorded under Comments.

e) Abnormalities in physiological testing or physical examination (findings that require clinical intervention or further investigation beyond ordering a repeat [confirmatory] test).

f) Laboratory abnormalities that require clinical intervention or further investigation (beyond ordering a repeat [confirmatory] test) unless they are associated with an already reported clinical event. Laboratory abnormalities associated with a clinical event (e.g., elevated liver enzymes in a patient with jaundice) should be described under Comments on the report of the clinical event rather than listed as a separate adverse event.

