#### Seriousness (Gravity)

Each adverse event is to be classified by the Principal Investigator as *Serious* or *Non-Serious*. This classification of the gravity of the event determines the reporting procedures to be followed.

A *Serious Adverse Event* (experience) or reaction is any untoward medical occurrence that at any dose results in:

- death
- life-threatening (Note: The term “life-threatening” in the definition of “serious” refers to an event in which the patient was at risk of death at the time of the event; it does not refer to an event which hypothetically might have caused death if it were more severe)
- in-patient hospitalization or prolongation of existing hospitalization
- persistent or significant disability/incapacity (any sight-threatening event with ophthalmic products is a significant incapacity)
- congenital anomaly / birth defect

Serious also includes any other adverse event that the investigator or the company judges to be serious, such as important medical events that may not be immediately life-threatening or result in death or hospitalization, but may jeopardize the patient or may require intervention to prevent one of the other outcomes listed in the definition above.

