# STATISTICAL METHODS PLANNED, AND DETERMINATION OF SAMPLE SIZE

## Statistical and Analytical Plan

The safety population includes all patients who have received any amount of ABR-215757.

The intention to treat population includes all patients who have received any amount of ABR-215757.

The Per Protocol population includes all patients without major protocol violations. Both populations will be described with regard to baseline data and exposure descriptively.

The adverse events, number of events and number of patients, will be summarized for the safety population by severity, by system organ class and by preferred term. Related AEs will be summarized in the same way.

Laboratory values including biomarkers, assumed to be log-normally distributed, will be summarized by visit, both absolute value and the ratio versus day 0 (n, mean, standard deviation, standard error, geometric mean with error and 95% confidence interval, median, min, max, quartiles and a p-value indicating if the value is significantly changed from baseline).

Disease activity variables, assumed to be normally distributed, will be summarized by visit, both absolute value and absolute change since day 0 (n, mean, standard deviation, standard error, 95% confidence interval, median, min, max, quartiles and a p-value indicating if the value is significantly changed from baseline). The time adjusted area under curve (AUC) will be calculated for the change from day 0 for the disease activity variables and will be summarized as above.

Vital signs and ECG will be summarized by visit as above shown for disease activity variables.

The correlation between selected variables (changes in disease activity variables and ratios versus day 0 for biomarkers) will be shown in figures. The Spearmann correlation coefficient will also be shown. Further analysis will be performed based upon the found correlations.

The screening value will be used in case the day 0 value is missing.

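### Where a medical condition causes an accident, the AE rule records the resulting injury under Comments, so the injury has no coded AE record of its own, contrary to the AE definition

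*Protocol*

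**What the plan says.** Protocol Section 5.5.3.1 (Definitions) opens broadly: an AE is "any untoward medical occurrence in a patient or clinical investigation subject administered a pharmaceutical product", whether or not the drug caused it. The list that follows includes, as item d, "Injury or accidents".

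A note within item d then deals with an injury or accident known to have a medical cause, using a fall after dizziness as its example. It states that "the medical condition (dizziness) and the accident (fall) should be reported as two separate adverse events", and it closes with "The outcome of the accident (e.g., hip fracture secondary to the fall) should be recorded under Comments".

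Three other places bear on how this is read:

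- **Item f of the same list** deals with laboratory abnormalities that accompany a clinical event. These "should be described under Comments on the report of the clinical event rather than listed as a separate adverse event".
- **The Procedures paragraph of Section 5.5.3.1** keeps procedures out of the AE record but requires the underlying condition to be reported if it qualifies as an AE. Its example reports the appendicitis and notes the appendectomy under Comments.
- **Section 6.1 (Statistical and Analytical Plan)** says that AEs, as numbers of events and of patients, "will be summarized for the safety population by severity, by system organ class and by preferred term". Related AEs are summarized in the same way. Comments text is not mentioned.

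**The concern.** In the protocol's own example the fracture is plausibly the gravest of the three occurrences, yet it is the only one with no AE entry. The site is told in one sentence that injuries are AEs and in another to put an injury in a comment. Sites may resolve this differently, or follow item d to the letter.

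At stake is the content of the safety tables. Safety and tolerability is the first of the secondary objectives, the study has a single arm, and the number of patients is small, so individual events are read one by one. A reader of the preferred-term table would see dizziness and a fall but not the injury, and the severity and relatedness shown would be those of the cause and the mechanism.

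**Working it through.** The plan gives no figure to reproduce. The check sets the passages against each other, using the protocol's own example of dizziness, fall and hip fracture.

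**1. Is the fracture an AE?**
- Under the general definition in Section 5.5.3.1: yes, as an untoward medical occurrence.
- Under the opening words of item d: yes, as an injury.
- Under the Procedures paragraph: yes, if the fracture leads to a procedure, because the condition behind a procedure must be reported when it meets the AE definition.
- Under the last sentence of item d: it goes to Comments, while two other occurrences are named as the AEs.

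Three rules point one way and one points the other. If the fracture is operated on, the Procedures paragraph calls for an AE entry and item d sends the same fracture to Comments.

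**2. Does Comments mean instead of an AE entry, or in addition to one?** Item f says outright that its Comments entry replaces a separate AE. The Procedures paragraph also uses Comments for something that is not an AE, namely the procedure. Item d lacks the explicit exclusion, but it counts exactly two AEs and gives the outcome a different destination. The natural reading is that Comments replaces the AE entry.

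**3. What reaches the Section 6.1 tables?**

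| Occurrence | AE record under item d | Own preferred term, severity, relatedness |
| --- | --- | --- |
| Dizziness | yes | yes |
| Fall | yes | yes |
| Hip fracture | no (Comments) | no |

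The episode yields 2 events and 1 patient. With the fracture as its own AE it would yield 3 events and still 1 patient.

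**4. Is seriousness lost?** No. Section 5.5.3.3 defines a serious event by what it results in, including "in-patient hospitalization or prolongation of existing hospitalization". A fall that results in hospitalization meets this, and the investigator or the company may also judge any AE serious.

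**5. Size.** Section 3.2 plans approximately 15 patients and at most 20, aiming for at least 10 who complete. The safety population is everyone treated. For one affected patient, the share missing from the injury's own line is:
- 1/20 = 5% at the maximum;
- 1/15 = 6.7% at the planned number;
- 1/10 = 10% only if no more than 10 patients were treated, since the 10 in Section 3.2 is a target for completers.

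These percentages concern one preferred term. The proportion of patients with any AE does not change, and the proportion with a serious AE does not change if the fall is classified as serious.

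**The case against.** A reader might infer that a serious injury does not count as an AE in this study and disappears from the safety data. The protocol does not support that. Item d lists injury as an AE, and only the outcome of a reported accident is displaced. The patient is counted, the fall and its cause are counted, and the fall can carry the serious classification. The causal condition, which matters most for attribution to the drug, keeps its own coded record.

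It can also be said that:

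- **The note is narrow.** It is written for accidents with a known medical cause. This stands. Whether its last sentence reaches other accidents is unclear, so it cannot be claimed that every accident loses its injury term.
- **Item d does not forbid an AE entry.** Unlike item f, it contains no exclusion, so a site could record the fracture both as an AE and under Comments. This is possible but strained, given the count of two AEs and the way Comments is used elsewhere in the section.
- **The Procedures paragraph captures a treated fracture.** It does where a procedure is performed, but by contradicting item d. It does not help where no procedure is done.
- **Comments may be coded or listed under other documents.** The protocol does not say, and a case report form guideline or analysis plan might. The consequence for the tables therefore rests on an assumption.
- **Folding an injury into its accident limits multiple counting.** That is a legitimate aim, but it does not remove the conflict with the AE definition.

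**Conclusion.** The point holds in limited form. For an accident caused by a medical condition, item d conflicts with the general AE definition, with its own opening words and, where a procedure follows, with the Procedures paragraph. Followed literally, it leaves the injury diagnosis without an AE record and hence without its own preferred term, severity or relatedness in the Section 6.1 tables. The episode and its seriousness remain captured through the fall and its cause.

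The effect is one missing term per such accident, or 5% to 6.7% of patients on that term's line for one affected patient among 20 or 15 treated. This assumes that Comments text is not separately coded and that sites take item d at its word. How many such accidents will occur cannot be told from the protocol, and there may be none. No biomarker result depends on the sentence. The severity is low, but the protocol fixes what sites record, and an analysis plan can tabulate only what was recorded and coded.

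**What to change.** Reconcile the passages by changing the last sentence of item d in Section 5.5.3.1. It should say that an injury resulting from an accident is reported as an AE in its own right, with its own seriousness, severity and relatedness, and is linked to the accident and to any causative condition. It should apply whether or not the accident had a medical cause, which also settles the scope of the note. Comments would then hold narrative only.

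The cost is one sentence in the protocol and a matching line in the case report form completion guideline, with no new procedure, visit or assessment. The small downside is that one episode can add more than one event to the event counts (3 instead of 2 in the protocol's example). The number of patients with at least one AE is unaffected, and the link between the records lets a reader see that they belong to one episode.

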***Pre-existing Conditions***

In this study, a pre-existing condition (i.e., a disorder present before the adverse event reporting period started and noted on the pre-treatment medical history/physical examination form) should not be reported as an adverse event unless the condition worsens or episodes increase in frequency during the adverse event reporting period.

***Procedures***

Diagnostic and therapeutic non-invasive and invasive procedures, such as surgery, should not be reported as adverse events. However, the medical condition for which the procedure was performed should be reported if it meets the definition of an adverse event. For example, an acute appendicitis that begins during the adverse event reporting period should be reported as the adverse event and the resulting appendectomy noted under Comments.

#### Adverse Event Reporting Period

The adverse event reporting period for this study starts at the first study related procedure after signing the Informed consent form and ends at the last scheduled study visit after the last dose of study medication.

All adverse events that occur in patients during the adverse event reporting period specified in the protocol must be reported to Active Biotech AB, whether or not the event is considered study medication related.

#### Seriousness (Gravity)

Each adverse event is to be classified by the Principal Investigator as *Serious* or *Non-Serious*. This classification of the gravity of the event determines the reporting procedures to be followed.

A *Serious Adverse Event* (experience) or reaction is any untoward medical occurrence that at any dose results in:

- death
- life-threatening (Note: The term “life-threatening” in the definition of “serious” refers to an event in which the patient was at risk of death at the time of the event; it does not refer to an event which hypothetically might have caused death if it were more severe)
- in-patient hospitalization or prolongation of existing hospitalization
- persistent or significant disability/incapacity (any sight-threatening event with ophthalmic products is a significant incapacity)
- congenital anomaly / birth defect

Serious also includes any other adverse event that the investigator or the company judges to be serious, such as important medical events that may not be immediately life-threatening or result in death or hospitalization, but may jeopardize the patient or may require intervention to prevent one of the other outcomes listed in the definition above.

